#### 2.6.1. Anthropometric and Physiological Measures

During each assessment, several measures were obtained including height, weight, hip, and waist circumference, resting blood pressure, resting heart rate, and fat percentage. Resting heart rate and resting blood pressure were measured alternately three times to improve measurement accuracy. Height and weight were assessed without shoes using a portable stadiometer of Martin (GPM anthropological instruments, Zurich, Switzerland) and a digital scale (Seca, Hamburg, Germany). BMI is calculated as body weight/height². The same measuring tape with tension rod was used for each waist and hip circumference measure. The waist was measured at the smallest circumference of the natural waist, just above the belly button. Hip circumference was assessed with the measuring tape being placed just above both iliac crests. Bioelectrical impedance analysis (BIA) was used to obtain a complete analysis of the body composition (percent distribution of body fat). All participants were measured by the same person.

#### 2.6.2. Physical Activity Assessment

Physical activity levels were assessed using the armband. The armband is a PA monitor that is worn on the upper left arm halfway between the acromion and olecranon processes. This device measures physical (in)activity using accelerometry technology augmented by two heat sensors (a thermistor-based skin surface sensor and a proprietary heat flux sensor) and a galvanic skin response sensor. These four internal sensors turn on the monitor (i.e., with skin contact) and estimate armband compliance, daily energy expenditure, step count, sleep efficiency, and the intensity, duration, and frequency of PA bouts. Collected PA data were downloaded during the baseline, 3-month, 6-month, and 12-month assessments. All armband data were analyzed by computer-based software (version 6.1) at 1-minute intervals using demographic information (i.e., gender, age, height, and weight at prior assessment) and proprietary algorithms. Throughout the study, the DG and CoachG group participants used the self-monitoring device to aid behavior change via real-time lifestyle feedback targeting PA.

 Baseline PA occurred over a one-year period (July 2010–July 2011) which makes it possible to account for seasonal variation in PA in a predominantly sedentary population.

#### 2.6.3. SenseWear Armband Validity

Independent researchers have validated the SenseWear system, especially with respect to comparing energy expenditure measurements from the Armband to estimates from gold-standard laboratory equipment [47–50]. An extensive review of the literature shows different validation studies where several SenseWear models (SenseWear, SenseWear pro, SenseWear pro2, and SenseWear pro3) and software algorithms are used. The SenseWear Armband has been validated as a measure of daily PA with findings suggesting that both minute-by-minutes as well as average energy expenditure can be a valid measurement of “free-living” activity [51, 52]. Previous validation studies have merely focused on low-to-moderate intensity activities. Two recent studies [53, 54] discussed the validation of the SWA at higher intensity levels and found a significant underestimation of the armband compared to indirect calorimetry for vigorous and very vigorous exercise intensities.

### 2.7. Statistical Analysis

Differences between the four study arms in PA outcomes will be tested according to the intention-to-treat philosophy. All participants' data will be analyzed according to their group assignment at randomization, regardless of adherence to the intervention. The PA outcomes being studied are daily energy expenditure (DEE), active energy expenditure (AEE), minutes of PA, physical activity level (PAL), and steps. A primary comparison is between the PA outcomes of groups who receive feedback (step group, display group and coaching group) and the group receiving no feedback (minimal intervention group). We hypothesize that getting feedback on the PA pattern will alter the PAL compared to having no information. Secondly, a comparison will be made on the difference in PA variables between participants who received feedback by means of the SWA display (display group) and participants who are only given information on their daily step count using a simple pedometer (step group). Since the SWA display gives more detailed information on different PA variables (minutes of PA, DEE, and steps) in contrast to the pedometer which only gives information on the daily step count, it is expected that people from the display group will have more benefits of the intervention compared to those belonging to the step group. Finally, the additional effect of a coach having weekly meetings with the participants will be evaluated. We hypothesize that the power of the interaction of a coach will result in an increase of the PA outcomes compared to subjects only receiving information by means of a technological instrument (display group and step group). Differences in PA outcome measures will be examined using analysis of covariance (ANCOVA) models of 12-month change scores. Self-reported PA, awareness, and cognitions will be analyzed as secondary outcomes. All analyses take into account specified covariates, including age, gender, BMI, education, percentage of armband wearing time, and baseline values of PA outcome measures. 

Based on our results from a pilot study (*n* = 52; PALpre = 1.41 ± 0.11 METs), an a priori power analysis was performed to determine the sample size necessary to detect a significant increase in energy expenditure in the intervention groups. Sample size calculations showed that 57 subjects in each group would give 80% power to detect a difference in PAL between baseline and posttest at a significance level of *P* < 0.05.

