## 2. Methods/Design

### 2.1. Study Design

We performed a 12-month randomized controlled trial in which we randomly assigned sedentary male (*n* = 103) and female (*n* = 124) employees to one of four intervention groups: a minimal intervention group received no feedback during the intervention period (MIG; *n* = 56); a pedometer group received information on their daily step count and received a step diary to write down their daily steps (PG; *n* = 57); a display group got personalized feedback by means of the SWA display and received a diary to write done their additional activities (DG; *n* = 57); a coaching group also received the display and diary and additionally had weekly meetings with a coach to discuss the progress they had made (CoachG; *n* = 57). During those meetings, the coach attempted to create an autonomy-supportive environment by encouraging choice and initiation (“how would you increase your activities this week?”), providing participants with different options (“maybe you could go for a walk during your lunch break or travel to work by bike?”), giving informational positive feedback, and acknowledging that the feeling of competence grows from feedback inherent to task (“well done, this week you participated at least more than one hour a day in PA”).

Outcome measures were assessed during a baseline assessment and again at 3, 6, and 12 months. The primary outcome of the study is the level of physical activity (PAL). Secondary outcome measures include step count, minutes of physical (in)activity (sedentary, light, moderate, vigorous, and very vigorous intensity PA), daily energy expenditure in PA, percentage of participants losing fat percentage, and stages of motivational readiness for PA.

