### 2.4. Randomization

After successfully completing the baseline measurement and signing the informed consent, eligible participants were randomized into one of the four groups. During the randomization visit, all participants received an evaluation of their baseline measurement. The feedback report also gave information about the benefits of an active lifestyle, the current PA recommendations, how to get active in daily life, and tips for starting PA.

Table 1 shows the descriptive statistics of our study population. Our population includes participants with a bPAL ≥ 1.71 MET (Act), individuals that dropped out from the intervention trial (DO), and the four intervention arms (MIG, PG, DG, and CoachG). The randomization process achieves a reasonable balance across the four intervention arms at baseline. After exclusion of the active group and the drop-out group, post hoc tests reveal a difference in bPAL between the PG and DG of 0.08 MET for the total group and 0.11 MET for the male group. No difference in bPAL exists between the PG and DG for the female group. 

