### 2.5. Followup Examinations

Followup data collection visits occurred at 3, 6, and 12 months after randomization and was collected between October 2010 and July 2012. The same measurements completed during the baseline session were assessed during each followup visit. Participants were also asked to fill in the FPACQ to assess detailed information on several dimensions of PA and sedentary behavior over a usual week. After each followup measurement, participants received feedback about their physical (in)activity level and a comparison was made with previous measurements.

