## 3. Intervention

### 3.1. Intervention Groups

All intervention groups receive a feedback report on the physical activity level, amount of steps taken, and minutes of physical (in)activity. In a personal contact with a coach, the report is discussed. The intervention study was executed by one coach to maximize the reliability of the intervention trial.

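### The primary hypothesis is worded as feedback versus no information, but the minimal intervention group also gets feedback, so the 12-month contrast estimates only what device-based feedback adds

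*Protocol article*

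**What the plan says.** **What is to be tested.** Section 2.7 sets the three feedback arms against "the group receiving no feedback (minimal intervention group" and gives the hypothesis as "We hypothesize that getting feedback on the PA pattern will alter the PAL compared to having no information". The Abstract also describes MIG as a group without feedback and sets no time limit. The analysis is an ANCOVA of 12-month change.

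**What every arm receives.**
- Section 2.4: "During the randomization visit, all participants received an evaluation of their baseline measurement". On content: "The feedback report also gave information about the benefits of an active lifestyle, the current PA recommendations", followed by practical advice on becoming active.
- Section 3.1: "All intervention groups receive a feedback report on the physical activity level, amount of steps taken, and minutes of physical (in)activity". Then: "In a personal contact with a coach, the report is discussed".
- Section 2.5: "After each followup measurement, participants received feedback about their physical (in)activity level and a comparison was made with previous measurements".

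**What is withheld from MIG.** Section 2.1: "a minimal intervention group received no feedback during the intervention period". Section 3.1.1 and the Figure 1 legend also confine the absence of feedback to the 4-week intervention period. Section 3.1.1 words it as nothing further, which implies that feedback came before.

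**The concern.** The hypothesis names a comparator that the trial does not have. MIG is told its activity level, steps and active minutes, is given recommendations, talks the report through with a coach, and is later shown how its results have moved.

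The article's own rationale treats such information as active. The Introduction argues that people consider change once they learn that they are inactive, and that returning activity data to a person can affect exercise behaviour at once. On that reasoning the control arm receives part of the ingredient under test.

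What is at stake is the primary conclusion. Read against section 2.7 as worded, a null result invites the statement that feedback does not work. A positive result invites the statement that feedback beats none. The design supports neither.

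**Working it through.** **1. Is MIG among those who receive the reports?** Section 2.4 says all participants. Section 3.1 says all intervention groups, and section 2.1 counts MIG as one of the four. Section 2.5 says participants and excepts no arm, so including MIG is its plain reading, although the arms are not named.

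**2. Which feedback can affect the 12-month outcome?** Only feedback given before that measurement.

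| Occasion | Source | Reaches MIG | Precedes 12-month measurement |
|---|---|---|---|
| Baseline report and coach discussion | 2.4, 3.1 | yes | yes |
| Feedback after 3-month measurement | 2.5 | yes | yes |
| Feedback after 6-month measurement | 2.5 | yes | yes |
| Feedback after 12-month measurement | 2.5 | yes | no |

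That makes three occasions in MIG. Section 2.5 describes feedback and a comparison with earlier results at follow-up. It does not mention a coach discussion there.

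**3. What does the contrast estimate?** Let R be the effect of the shared reports and feedback, D the effect of the device (and coaching), and I any overlap between them.
- Mean change in the feedback arms: background + R + D − I
- Mean change in MIG: background + R
- Contrast: D − I
- Feedback versus no information: T = R + D − I

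The contrast differs from T by R. If R is positive, it understates T. If effects are additive (I = 0), the contrast is exactly D and is unbiased for the added device effect.

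**4. Can the plan's sample size be used to size this?** Section 2.7 gives 57 per group, 80% power, P < 0.05 and a pilot SD of 0.11, but no target difference, so 57 cannot be reproduced forward. Solved backwards for two groups, two-sided: (1.960 + 0.842) × 0.11 × √(2/57) = 0.058. This neither confirms nor refutes 57, and the point does not depend on it.

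**5. Illustration of the shortfall against T (assumptions, not findings).** Assume T = 0.10. That is the individual goal in section 3.1.3, not an expected difference between arms. Assume also that reports account for a share s of T, so the contrast is (1 − s) × 0.10. The feedback arms pool to 57 + 57 + 57 = 171, against 56 in MIG. Two-sided power = Φ[contrast / (SD × √(1/171 + 1/56)) − 1.96], with √(1/171 + 1/56) = 0.154. SD 0.11 is the pilot value. SD 0.16 is close to the arm SDs of baseline PAL in Table 1 (0.15 to 0.17).

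| s | Contrast | Power, SD 0.11 | Power, SD 0.16 |
|---|---|---|---|
| 0 | 0.100 | 1.00 | 0.98 |
| 0.25 | 0.075 | 0.99 | 0.86 |
| 0.50 | 0.050 | 0.84 | 0.53 |

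Both SDs are cross-sectional. The planned model adjusts change for baseline, and the article gives no residual SD for it.

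**The case against.** The strongest reply is that the article already carries the narrower meaning. The arm is called a minimal intervention, not an untreated control. Sections 2.1 and 3.1.1 and the Figure 1 legend tie the absence of feedback to the intervention period. The hypotheses in the Abstract and Introduction compare with the minimal intervention group, and the Discussion speaks of real-time feedback. The shared reports are openly described. All of this stands. It shows that the design is coherent and that the fault lies in the wording of the Abstract and section 2.7. It does not remove the fault, because section 2.7 is where the primary hypothesis for the analysis is stated.

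Three stronger readings are tempting and are not supported.
- *The trial's effect is biased toward zero.* This holds only against a no-information target, or if report and device effects overlap. Under additivity, what all arms share cancels.
- *Power collapses to about one half.* That is the worst cell of an assumed grid. At the pilot SD the same cell is 0.84, and the documents support neither the share nor the 0.10.
- *The 3-month contrast recovers feedback versus none.* It precedes any follow-up feedback, as does the armband week after the 4-week period. Both still follow the baseline report and coach discussion in every arm.

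**Conclusion.** The point stands as a misstatement of the primary comparison, not as a flaw in randomisation, data or model. The 12-month contrast validly estimates what pedometer or display feedback, with or without weekly coaching, adds to the baseline report and periodic follow-up feedback. It cannot answer the question of feedback versus no information.

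Against that wider question it would probably understate the effect, by the effect of the shared reports. The documents give no figure for this. The conclusion rests on the plain reading of section 2.5 that MIG is included. Without section 2.5, the baseline report and discussion in sections 2.4 and 3.1 alone would still rule out the label of no information.

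**What to change.** In the Abstract and section 2.7:
- Describe the primary comparison as device-based self-monitoring feedback (with or without coaching) added to the baseline report and periodic follow-up feedback, versus that report and feedback alone.
- Remove the reference to having no information, and limit the statement that MIG had no feedback to the 4-week intervention period, as section 2.1 does.
- State that a null 12-month result is not evidence that feedback as such is ineffective.

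The Discussion does not use the no-information wording and needs no correction on this point. The duration of display use should stay out of the new wording until section 2.6.2 (use throughout the study) and section 3.1.3 (display returned after 4 weeks) are reconciled.

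Optionally, report the 3-month contrast as supportive, noting that it precedes follow-up feedback but not the baseline report and discussion. If power under dilution is mentioned at all, show the whole assumed range with its conditions.

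The cost is wording and, if wanted, one contrast at a time point already scheduled. The claim becomes narrower.

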The coaching is based on the SDT of Deci and Ryan. This theory states that the extent that the environment allows one to experience feelings of competence, autonomy, and relatedness will influence the person's motivation toward a given task. The behavior of a coach has a strong impact on people's needs being satisfied and, in turn, on their motivation being optimal or not. It can be speculated that if the relation with a coach leads to relatedness satisfaction, the message and values transmitted by the coach may be more readily internalized by the participant. Furthermore, to the extent that the coach also supports the client's autonomy, such internalization will be autonomous in nature, thereby leading to positive and long-lasting PA changes in the participant. Our intervention study wants to determine the effectiveness of continuous self-monitoring and real-time feedback from the SenseWear Armband alone and in combination with a weekly meeting with a personal coach. We hypothesize that the weekly meeting with a coach will help create an autonomous supportive environment and stimulate the feeling of relatedness. 

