#### 3.1.2. Pedometer Group

The pedometer group (26 male, 31 female) receives feedback on the daily step count by means of a pedometer (Yamax Digiwalker, SW200) and wears the SenseWear Armband for measuring the physical activity level. The Yamax SW Digiwalker is a waist-mounted device and is the most widely used pedometer in research studies. Previous studies comparing 10 or more pedometer models identified it as one of the most accurate and reliable electronic pedometers available [14]. Every day participants of the pedometer group write down their amount of steps in a step diary and also mention the reason for walking 10,000 steps a day. After an intervention period of 4 weeks, the pedometer is returned and participants are asked to wear the SenseWear Armband for one more week without knowing the amount of steps taken every day.

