#### 3.1.4. Coaching Group

The coaching group (26 male, 31 female) receives the same intervention as the display group (see above) but additionally has a weekly meeting with a coach to discuss the progress they have made. The session format is as follows: check-in of SenseWear data, discussion of results, evaluation of the individual goal setting, summary of current session, and preview of the next session.

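### The coach's added effect is set against the display and pedometer groups together, so the contrast also carries part of the display-versus-pedometer effect; only CoachG minus DG isolates the coach

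*Protocol article*

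**What the plan says.** Section 2.7 lists three comparisons on the physical activity outcomes, all under ANCOVA of 12-month change.

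- **First:** "groups who receive feedback (step group, display group and coaching group") against the minimal intervention group.
- **Second:** display against pedometer (called the step group in this section). The direction is predicted: "it is expected that people from the display group will have more benefits of the intervention compared to those belonging to the step group".
- **Third:** the coach. The target is stated as "Finally, the additional effect of a coach having weekly meetings with the participants will be evaluated", and the hypothesis is that coached participants will increase their activity "compared to subjects only receiving information by means of a technological instrument (display group and step group").

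The arms are described in section 3.1. The coaching group "receives the same intervention as the display group (see above) but additionally has a weekly meeting with a coach". The pedometer group "receives feedback on the daily step count by means of a pedometer (Yamax Digiwalker, SW200") and has no SenseWear display. Section 3.1.3 gives the display group individual targets for calories, steps and active minutes, and the coaching group shares these.

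The Introduction frames the coaching question as the effectiveness of "real-time feedback from the SenseWear Armband alone and in combination with a weekly meeting with a personal coach". Section 2.7 names no separate comparison of CoachG with DG.

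**The concern.** The stated target and the stated comparator do not match. The display group differs from the coaching group by the coach alone. The pedometer group differs by the coach and also by the device, the content of the feedback and the individual targets. Putting the pedometer group in the comparator therefore adds part of the display-versus-pedometer effect to what is reported as the coach's effect.

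The plan itself predicts that this added part is positive. If the second hypothesis is true, the third contrast is biased upward, and a significant result could not be credited to the coach. If the pedometer turned out better than the display, the same contrast would hide a coach who works. Covariate adjustment, including for baseline PAL, does not help, because the extra term is a difference between treatments and not a baseline imbalance.

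**Working it through.** **Inputs from the document**

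- 57 participants in each of PG, DG and CoachG (section 2.1, Table 1).
- Significance level 0.05 (section 2.7). Sidedness is not stated; two-sided is assumed.
- SD of PAL: 0.11 in the pilot (section 2.7); 0.15 to 0.17 at baseline across the four arms (Table 1), taken as 0.16.

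**Inputs that must be assumed**

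- D, the true DG minus PG difference. None is given. The range used is 0 to 0.10; the top equals the individual PAL goal in section 3.1.3, the only PAL increment in the document.
- The SD of 12-month change. None is given; 0.11 and 0.16 stand in for it.

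**The plan's own figure.** Section 2.7 says "57 subjects in each group would give 80% power" for a baseline-to-posttest difference. It states no size of difference, so 57 cannot be reproduced. Solving backwards at SD 0.11, 57 per arm corresponds to a between-arm difference of 0.11 × (1.960 + 0.842) × √(2/57) = 0.058. If the SD of change is also 0.11, it corresponds to a within-group change of 0.11 × 2.802/√57 = 0.041. Neither supplies a value for D.

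**Step 1: what the contrast estimates.** Let c = CoachG − DG (the coach) and D = DG − PG. Then

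CoachG − (DG + PG)/2 = (CoachG − DG) + ½(DG − PG) = c + D/2.

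The bias D/2 does not depend on the SD. If the sentence means two separate comparisons, CoachG − DG = c is clean, but CoachG − PG = c + D carries the whole difference.

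**Step 2: standard errors**

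- Pooled comparator: SD × √(1/57 + 1/114) = 0.1622 × SD, which is 0.0178 (SD 0.11) or 0.0260 (SD 0.16).
- CoachG versus DG: SD × √(2/57) = 0.1873 × SD, which is 0.0206 or 0.0300.
- Ratio: 0.1873/0.1622 = 1.155.

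**Step 3: chance of declaring a coach benefit when c = 0.** For the pooled contrast this is 1 − Φ(1.96 − (D/2)/SE).

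| D | Bias D/2 | SD 0.11 | SD 0.16 |
|---|---|---|---|
| 0 | 0 | 2.5% | 2.5% |
| 0.02 | 0.01 | 8.1% | 5.8% |
| 0.04 | 0.02 | 20.1% | 11.7% |
| 0.06 | 0.03 | 39.0% | 21.1% |
| 0.08 | 0.04 | 61.1% | 33.8% |
| 0.10 | 0.05 | 80.0% | 48.7% |

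Example at D = 0.06, SD 0.11: 0.03/0.0178 = 1.68, and 1 − Φ(0.28) = 39%. Simulation of 100,000 trials gave 38.7% there and 79.4% at D = 0.10 with SD 0.11; at SD 0.16 it gave 20.8% and 48.2%. In the same simulations CoachG versus DG stayed at 2.5% throughout.

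**Step 4: the opposite sign.** With a real coach effect c = 0.06 and D = −0.06, the pooled contrast has expectation 0.06 − 0.03 = 0.03. Its power is 39% against 83% for CoachG versus DG at SD 0.11, and 21% against 52% at SD 0.16.

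**Step 5: what pooling buys if D = 0.** The difference detectable with 80% power is 0.050 pooled against 0.058 for CoachG versus DG (SD 0.11), or 0.073 against 0.084 (SD 0.16).

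**The case against.** **Pooling is inferred.** Section 2.7 gives no contrast weights and never says the two groups are combined. The sentence could mean that CoachG exceeds DG and also exceeds PG, and a four-arm ANCOVA would yield CoachG minus DG directly. Exact coefficients may sit in an analysis plan that is not shown. This stands as a limit on certainty: a reader might infer that the document states a pooled test, and it does not. But the comparator is named, not omitted. Naming two arms as one class of subjects reads most naturally as pooling, and under the other reading the CoachG-versus-PG half still does not isolate the coach.

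**The contaminating term is visible.** DG versus PG is itself a planned comparison, so a careful reader could see that half of it sits in the coach contrast. That is true, but it does not make the contrast a test of the coach.

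**The large percentages need a large D.** A difference of 0.10 at 12 months would require the display to beat an active 10,000-step programme by the whole individual goal, although both devices are handed back after 4 weeks. The 0.08 baseline gap between PG and DG in section 2.4 is not a treatment effect and gives no support for a D of that size. This stands. At D = 0.02 the false-benefit rate is only about 6% to 8%, so the upper figures are not a forecast.

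**The primary contrast.** A reader might infer that the feedback-versus-no-feedback contrast has the same fault, because CoachG on its feedback side also gets coaching. The document does not support that. CoachG does receive feedback, the abstract and section 2.7 both include it in the declared primary hypothesis, and removing it would change the primary question.

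**Conclusion.** The point holds for the coaching contrast. The comparator named in section 2.7 does not match the target stated there, nor the framing in the Introduction. Under the natural pooled reading the contrast is biased by D/2, upward if the plan's second hypothesis is right and downward if PG does better than DG. With no coach effect, the chance of a declared benefit is about 6% to 49% (SD 0.16) or 8% to 80% (SD 0.11) for D from 0.02 to 0.10, against a nominal 2.5% in that direction. If D is zero the contrast is unbiased and somewhat more precise.

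The algebra rests only on the arm descriptions. The percentages rest on assumed values of D and of the SD of 12-month change, on a two-sided 5% test and on the pooled reading. The randomization, the data collected and the primary contrast are unaffected.

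**What to change.** In section 2.7, define the coach's added effect as CoachG minus DG, estimated from the four-arm ANCOVA of 12-month change. Any comparison of CoachG with DG and PG together should be labelled descriptive and named for what it is: coach plus display versus device feedback in general. Leave the primary feedback-versus-no-feedback contrast as written.

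The change rewords one contrast and needs no new data. The cost is precision: 57 versus 57 replaces 57 versus 114, so the standard error rises by about 15%, and the difference detectable with 80% power rises from 0.050 to 0.058 (SD 0.11) or from 0.073 to 0.084 (SD 0.16).

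### The contrast labelled as the additional effect of a coach sets the coaching group against the display and pedometer groups, so it can credit coaching with a benefit of the display

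*Protocol article*

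**What the plan says.** Section 2.7 (Statistical Analysis) sets out three comparisons, in this order:

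1. The feedback arms against the minimal intervention group (MIG). This one is called primary.
2. DG against PG, which the section calls the step group. Here "it is expected that people from the display group will have more benefits of the intervention compared to those belonging to the step group".
3. The coach question: "the additional effect of a coach having weekly meetings with the participants will be evaluated". The hypothesis is that physical activity outcomes will rise in CoachG "compared to subjects only receiving information by means of a technological instrument (display group and step group").

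The arms are described in section 3.1:

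- Section 3.1.4: CoachG "receives the same intervention as the display group (see above) but additionally has a weekly meeting with a coach".
- Section 3.1.2: PG "receives feedback on the daily step count by means of a pedometer (Yamax Digiwalker, SW200") and keeps a step diary.
- Section 3.1.3: DG has the display, an activity diary and individual goals for calories, steps and active minutes.

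The Introduction states the coach aim as the "effectiveness of continuous self-monitoring and real-time feedback from the SenseWear Armband alone and in combination with a weekly meeting with a personal coach". That is DG against CoachG.

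**The concern.** To isolate the coach, the comparator should match CoachG in everything except the meetings. Only DG does. PG also lacks the display, the calorie feedback and the goals for energy expenditure and active minutes. Placing PG in the comparator brings part of the display-versus-pedometer difference into an estimate that is labelled as the coach effect.

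Randomisation and covariate adjustment do not remove this, because it is a difference in treatment and not in the participants. If the display works better than the pedometer, as the plan expects, the error favours coaching. If the pedometer works better, a real coach effect is diluted. The question concerned is the final aim named in the Discussion and the reason for one of the four arms.

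**Working it through.** **Inputs from the article**

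- Arm sizes: PG 57, DG 57, CoachG 57 (Abstract, Table 1).
- Pilot SD of baseline PAL: 0.11 (section 2.7).
- Baseline PAL SDs of the four randomised arms: 0.15 to 0.17 (Table 1).
- Display group's individual energy goal: a PAL increase of 0.10 MET (section 3.1.3).
- Significance level: 0.05. Sidedness is not stated, and two-sided is assumed here.

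**Not given, so assumed**

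- Residual SD of the 12-month PAL change: 0.11 to 0.16, with 0.20 as a sensitivity case.
- True DG − PG: 0.02, 0.05 and 0.10. The last is an upper illustration only.

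**The plan's own figure.** Section 2.7 says that "57 subjects in each group would give 80% power to detect a difference in PAL between baseline and posttest". No detectable difference is stated, so the 57 cannot be reproduced. Solved backwards with SD 0.11, 57 per group detects (1.960 + 0.842) × 0.11 × √(2/57) = 0.058 between two arms, or (1.960 + 0.842) × 0.11/√57 = 0.041 within one arm. The point below does not depend on this.

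**Step 1: what the combined contrast estimates.** With equal arms, DG and PG each have weight one half:

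CoachG − (DG + PG)/2 = (CoachG − DG) + (DG − PG)/2

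The first term is the coach effect. The second is half of the quantity in the plan's second hypothesis.

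**Step 2: standard errors.**

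- Combined comparator: SD × √(1/57 + 1/114) = 0.162 × SD, which is 0.0178 at SD 0.11 and 0.0260 at SD 0.16.
- CoachG versus DG: SD × √(2/57) = 0.187 × SD, which is 0.0206 and 0.0300.
- Ratio: √(4/3) = 1.155.

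**Step 3: chance of a significant coach finding when the coach effect is zero.** Let b = (DG − PG)/2. Then P = 1 − Φ(1.96 − b/SE) + Φ(−1.96 − b/SE).

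| DG − PG | b | SD 0.11 | SD 0.16 | SD 0.20 |
|---|---|---|---|---|
| 0 | 0 | 5% | 5% | 5% |
| 0.02 | 0.010 | 8.7% | 6.7% | 6.1% |
| 0.05 | 0.025 | 28.8% | 16.1% | 12.0% |
| 0.10 | 0.050 | 80.0% | 48.7% | 33.8% |

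A simulation with t tests (40,000 runs per setting) gave 28.7% and 80.0% at SD 0.11 and 15.7% and 48.0% at SD 0.16, for DG − PG of 0.05 and 0.10. CoachG versus DG stayed between 4.7% and 5.1% throughout.

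**Step 4: the opposite direction.** Take a true coach effect of 0.058 and DG − PG = −0.05. The combined contrast then has expectation 0.058 − 0.025 = 0.033. Its power is 46% at SD 0.11 and 25% at SD 0.16. With DG − PG = 0 it would be 90% and 61%.

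**Step 5: the pairwise reading.** If the sentence means CoachG versus DG and CoachG versus PG separately, the second test carries all of DG − PG. With SE = 0.187 × SD and no coach effect, it is significant in 39–68% of trials at DG − PG = 0.05 (SD 0.16 to 0.11).

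**The case against.** - **Pooling is not stated.** Section 2.7 never says that the display and step groups are averaged, and the sentence could mean two pairwise tests. This stands as a caveat. However, the text describes one class of comparator, participants who receive only technological feedback, and the primary comparison lists its groups in the same way. Under the pairwise reading CoachG versus DG would be among the tests, but nothing names it as the one that measures the coach, and the other carries the whole display difference.
- **Contrast coding belongs in an analysis plan.** Exact coding often does. Here the article states the comparator, and it does not match the article's own aim.
- **Coaching versus technology alone is a fair question.** It is, as a comparison of packages. It is not the added effect of the coach.
- **A reader might infer that the coach question cannot be answered, or that the trial's main result is compromised.** The article supports neither. The primary comparison does not use this contrast. The coach effect can be recovered from the same four arms, as the third contrast minus half of the second.
- **A reader might take the 49–80% as the expected error rate.** The article does not support that. The 0.10 MET is a goal for the individual during a 4-week intervention, not a difference between arms at 12 months. The devices are returned after 4 weeks, and PG is itself an active arm. The SD of 12-month change is not given, and a larger one lowers the figures.
- **The test itself is not miscalibrated.** Correct. When DG and PG differ, the null hypothesis of the combined contrast is false. The error is to attribute the result to the coach.

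**Conclusion.** The point holds as a mismatch between a contrast and its label in the third planned comparison. On the natural reading, the contrast for the coach contains half of the display-versus-pedometer difference. On the pairwise reading, one of the two tests contains all of it. Since the plan expects that difference to be positive, its own hypotheses imply a coach estimate that is too high.

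The algebra needs only the arm descriptions and equal arm sizes. The weight of one half is exact at 57 per arm and would shift slightly if unequal numbers were analysed at 12 months. The size is conditional on figures that the article does not give: the inflation is slight if DG − PG is near 0.02, material at 0.05, and large only at the 0.10 illustration.

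**What to change.** In section 2.7, define the coach contrast as CoachG versus DG, estimated from the four-arm ANCOVA. If the comparison of CoachG with DG and PG together is kept, describe it as coach plus display versus device-only feedback, and do not report it as the effect of the coach.

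This is a change of wording, with no new data or participants. The cost is precision. The standard error of the coach contrast rises by about 15%, so the difference detectable with 80% power goes from 0.050 to 0.058 at SD 0.11, or from 0.073 to 0.084 at SD 0.16. The precision given up was available for the coach effect only on the assumption that DG and PG do equally well, which the plan's second hypothesis denies.
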